## Abstract

**Introduction::**

Re-irradiation after radiotherapy is a common treatment for locally recurrent esophageal cancer. However, the side effects of re-irradiation are serious. The most serious adverse reactions of re-irradiation include esophageal perforation and hemorrhage caused by esophageal perforation. Studies have shown that pulsed low-dose rate radiotherapy (PLDR) induces a hypersensitivity effect on tumor tissue and a hyper-repair effect on normal tissue, which can simultaneously reduce damage on the normal tissue and increase the therapeutic effect on the tumor. The objective of this study is to explore whether PLDR can reduce rate of esophageal perforation and improve efficacy in patients with recurrent esophageal squamous cell carcinoma (ESCC) after radiotherapy.

**Methods and analysis::**

This study is a prospective, multi-center, open, single-arm clinical trial designed to enroll 27 patients with locally recurrent ESCC after radiotherapy with or without chemotherapy. Re-irradiation will be performed using intensity modulated radiation therapy in 50 Gy/25 fractions. The strategy of PLDR includes dividing 2 Gy into 10 fractions, and administering each irradiating dose of 20 cGy at an interval of 3 minutes before the next low-dose irradiation. The actual dose rate of administration each time will be 16.67 cGy /minute. The primary endpoint in this study is the rate of esophageal perforation. The secondary endpoints are the objective remission rate, the palliative effect on quality of life and pain, and the time of disease progression. The observation time is 2 years after the end of the study.

**Trial registration::**

Clinical trial number: ChiCTR1900020609.

## Introduction

1

Esophageal cancer (EC) is a common malignant tumor, and ranks seventh in incidence and sixth in mortality worldwide. According to 2018 statistics data, there have been 572,000 new cases of esophageal cancer and 509,000 deaths.^[1]^ Esophageal squamous cell carcinoma (ESCC) is the most common histological type globally, especially with a high incidence in developing countries.^[2]^ In China, EC ranks third in incidence and mortality, and more than 90% of the EC cases are reported with ESCC.^[3–4]^ Concurrent chemoradiotherapy is the standard treatment for locally advanced ESCC in patients who are resistant to or unsuitable for surgical treatment. About 50% of the ESCC cases are reported to recur locally within 3 years after chemoradiotherapy, and most recurrences occur in the target area of gross tumor volume (GTV).^[5,6]^ Most patients with recurrence die within 1 year without treatment. At present, there is no standard treatment for local recurrence after radiotherapy. Common treatment methods include surgery, re-irradiation, chemotherapy, and supportive treatment. The proportion of patients receiving esophagectomy after recurrence is very small. According to data from Anderson Cancer Center, definitive chemoradiation failed in 184 of the 276 patients treated, while only 23 (8%) underwent esophagectomy.^[7]^ In general, re-irradiation is superior to other treatments in patients who cannot be treated with esophagectomy.^[8–11]^ Re-irradiation is limited by the tolerance dose of normal tissues in the lungs, spinal cord, and esophagus and hence, increasing the target dosage is difficult. Re-irradiation can increase the risk of adverse reactions, such as esophageal perforation, hemorrhage, and radiation pneumonia. The most serious adverse reaction is esophageal perforation with an incidence of approximately 30%.^[9,12]^

Low-dose rate radiation is considered effective to alleviate the side effects of radiotherapy. According to the classical cell survival curve of hypersensitivity (Fig. 1),^[13]^ hypersensitivity (HRS) is observed in tumor cells exposed to <0.2 Gy low dose rate irradiation with a steeper slope of survival curve (αs) than that of higher dose irradiation(αr). When the dose reaches 0.2 to 0.8 Gy, radiosensitivity began to shift from sensitivity to irradiation resistance (IRR). An interval between each pulse exists during pulsed low-dose rate radiotherapy (PLDR). Sufficient interval time can promote repair of normal tissues and reduce side effects on normal tissues thereby increasing the therapeutic effect on tumors and reducing damage on normal tissues.

**Figure 1 F1:**
[figure not shown]
Classical cell survival curve of hypersensitivity. αr = the slope of survival curve of higher dose irradiation; IRR: irradiation resistance, αs = the slope of survival curve of low dose rate irradiation, HRS = Hypersensitivity.

Researchers found that PLDR was more effective and exhibits lower toxicity to normal tissues than conventional radiotherapy in mouse models.^[14]^ The main reason for this is that PLDR causes less vascular damage, and retaining vascular network can improve tumor oxygenation. Normal tissue can be repaired during the treatment interval. Clinical studies of recurrent breast cancer, head and neck cancer, and glioma after radiotherapy have further demonstrated the effectiveness and safety of PLDR re-radiotherapy, and PLDR shows an increase in the ability to protect normal tissues.^[15–18]^ However, clinical studies of PLDR in patients with ESCC do not exist. Based on the effects of low dose radiosensitivity and low dose hyperrepair, we designed this study to explore whether intensity modulated radiation therapy (IMRT)-PLDR can reduce rate of esophageal perforation and improve efficacy in patients with recurrent esophageal squamous cell carcinoma (ESCC) after radiotherapy.

## Methods/design

2

### Recruitment and study design

2.1

This study is a prospective, multi-center, open, single-arm phase II clinical trial designed to enroll 27 patients with locally recurrent ESCC after radiotherapy with or without chemotherapy (Fig. 2). Before the start of treatment, each eligible patient will be fully explained the ethics, purpose, design, implementation, requirements, and timing of the study.

**Figure 2 F2:**
[figure not shown]
The clinical trial plan.

### Objectives

2.2

1.Primary endpointRate of esophageal perforation2.Secondary endpoints•Objective remission rate (ORR)•Palliative effect on quality of life and pain•Time of disease progression (TTP)

### Inclusion criteria

2.3

1.Age, 18 to 75 years;2.Pathological confirmation of ESCC;3.Local recurrence and/or lymph node metastasis in the irradiation field of first radiotherapy and life expectancy of >3 months;4.No distant metastasis;5.Eastern Cooperative Oncology Group (ECOG) score of 0 to 2, which measures the patient's physical condition;6.Patients who cannot tolerate surgery or the tumor cannot be removed surgically;7.The patient is conscious and capable of coordination with positioning and treatment;8.Availability of previous radiotherapy information, including total dose in the target area, segmentation mode, dose distribution, irradiation dose to normal tissue and isodose curve, can be obtained;9.The patient has a measurable solid tumor (response evaluation criteria: RECIST 1.1); Women of childbearing age must be in a non-pregnancy state (pregnancy test negative), menopausal women with menopause for >12 months and considered infertile, women of childbearing age who have taken effective contraceptive measures to prevent pregnancy during the study period and 3 months after the end of the study;10.Absolute neutrophil count (ANC) > 1.0 × 10^9^/L; Platelet (PLT) count – 75 × 10^9^ or higher/L;11.Patients must sign a written informed consent and be willing to participate in and complete the study and follow up.

### Exclusion criteria

2.4

1.patients with other malignant tumors;2.patients who received radiotherapy for the target area within 4 weeks before entering this study;3.patients with previous history of ataxia due to telangiectasia or other radiosensitivity reactions;4.patients with scleroderma or active connective tissue disease;5.patients with serious and uncontrollable infectious diseases;6.Patients with severe mental or psychological disorders, central nervous system disorders, cardiovascular and cerebrovascular complications, epilepsy and other diseases which may limit their understanding, implementation, and treatment compliance of informed consent.

### Subject withdrawal criteria

2.5

Criteria that will lead to the drop-out of a patient before completion of this study may be treatments for medical reasons or impairment that will result in an interruption or early completion of treatment, including:

1.Patient safety events;2.Any other physical condition that researchers suspect to increase the risk of radiation-related toxicity;3.Subjects voluntarily withdraw informed consent and request withdrawal from the clinical trial;4.Disease progression with medical imaging evidence (such as CT, MRI, B-mode ultrasonography, etc.) or clinical progress judged by researchers (the cause of progress needs to be recorded in detail);5.Pregnancy events during the study;6.Other researchers consider it necessary to withdraw from the study (the reasons for withdrawal need to be documented in detail);7.Patient participated in other clinical studies during this study;8.Inadequate patient compliance.

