### Assessment of the primary and secondary endpoints

2.8

Rate of esophageal perforation is the primary endpoint in this study, which will be observed from the initiation of re-irradiation to 60 days after the end of the study. Esophageal perforation should be diagnosed by esophageoscope. ORR is one of the secondary endpoints in our study. Ninety days after the end of treatment, we will evaluate the efficacy by using the RESICT 1.1 criterion through CT scan and esophageoscope. Quality of life scale QLQ-C30 (V3.0) according to the European Organization for Cancer Research and Treatment (EORTC) and digital pain scale will be assessed to determine the palliative effect on quality of life and pain in 2 years after the end of the study. Kaplan Meier curves will be performed to evaluate TTP, 2 years after the end of the study.

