### Statistical analysis

2.9

The power of the test is 80% and α = 0.05. According to the literature, the incidence of esophageal cancer perforation after re-irradiation is 30%. It is expected that after re-irradiation with PLDR technology, the rate of esophageal perforation will decrease to 10%. The optimal sample size for re-irradiation is 27 cases by checking the table (β = 0.20, α = 0.05).^[19]^ The proportion of patients with clinical response and the 95% confidence intervals will be calculated and reported. The Chi-Squared test and Kaplan–Meier method will be used to analyze the rates and severity of disease progression according to NCI-CTCAE (version 4), and Fisher exact probability test will be used to analyze the correlations between clinical outcomes and toxicity.

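### Section 2.5 does not separate stopping treatment from leaving the study, so patients can be withdrawn for reasons related to perforation before the primary window closes

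*Protocol article*

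**What the plan says.** Section 2.5 of the protocol article (Subject withdrawal criteria) opens with "Criteria that will lead to the drop-out of a patient before completion of this study". The same sentence describes these as medical reasons or impairment that interrupt treatment or end it early. Eight criteria follow. Four matter here:

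- Criterion 1: "Patient safety events", not defined further.
- Criterion 2: "Any other physical condition that researchers suspect to increase the risk of radiation-related toxicity".
- Criterion 4: "Disease progression with medical imaging evidence", or clinical progression in the researchers' judgement.
- Criterion 6: any other case in which the researchers think withdrawal necessary, with the reason documented.

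Section 2.8 names the perforation rate as primary and gives its window: "which will be observed from the initiation of re-irradiation to 60 days after the end of the study". Diagnosis is by esophagoscopy. The Introduction places perforation among the toxicities of re-irradiation: "The most serious adverse reaction is esophageal perforation with an incidence of approximately 30"%. The trial is open and single-arm (section 2.1).

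The article does not say whether a patient who meets a section 2.5 criterion is still observed for perforation, or how that patient counts in the primary rate.

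**The concern.** Section 2.5 uses one list for two different events: the end of protocol treatment and departure from the study. For a safety endpoint they must be kept apart, because a patient who stops treatment remains at risk of perforation.

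Criterion 2 is the sharpest case. It lets an investigator who knows the treatment withdraw a patient because a radiation toxicity seems more likely, and the primary endpoint is a radiation toxicity. Criteria 4 and 6, and safety events that come before any perforation, leave similar room. If withdrawn patients are not followed, loss from observation depends on the risk of the event being counted. The error then runs mainly one way: fewer perforations are seen, which favours PLDR. With no control arm, the comparison with the historical 30% absorbs the whole bias. An analysis plan can fix the denominator afterwards, but it cannot recover perforations that nobody looked for.

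**Working it through.** **Inputs.** From section 2.9: historical perforation rate 30% ("the incidence of esophageal cancer perforation after re-irradiation is 30"%), target 10%, α = 0.05, power 80%, n = 27. The share f of true perforators who are withdrawn and lost before their event is seen is not in the documents. It is assumed to be 10%, 20% or 30%.

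**The plan's own figure.** A sample size of 27 reproduces. For perforation-free rates of 0.70 against 0.90, the Simon optimal two-stage design has 6 patients in stage 1 and 27 in total. It continues with at most 1 perforation in 6 and succeeds with at most 4 in 27 (α = 0.0492, power 0.804). The exact single-stage one-sided minimum is close, at 28. The article states neither a two-stage rule nor a cut-off, so the limits below are reconstructions.

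**Limit used.** For a single-stage exact one-sided test at 5% with n = 27 and p = 0.30, P(X ≤ 3) = 0.020 and P(X ≤ 4) = 0.059. The largest limit that keeps to 5% is therefore 3.

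**Scale.** At 30%, 27 × 0.30 = 8.1 perforations are expected. The expected number lost is 8.1 × f: 0.8, 1.6 or 2.4 patients.

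**Case A: lost perforators counted as event-free.** The observed rate is 0.30 × (1 − f), the denominator stays 27, and X ~ Binomial(27, 0.30(1 − f)).

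**Case B: lost perforators dropped from the denominator.** The number removed is Binomial(27, 0.30f). Among the M who remain, the rate is 0.30(1 − f)/(1 − 0.30f). Each M is tested exactly at 5% against 30% (limit 3 for M = 24 to 27, limit 2 for M = 19 to 23), and the rejection probability is averaged over M.

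| f | Rate, A | P(≤3 of 27), A | Rate, B | Type I error, B |
|---|---|---|---|---|
| 0 | 0.300 | 2.0% | 0.300 | 2.0% |
| 10% | 0.270 | 4.2% | 0.278 | 4.2% |
| 20% | 0.240 | 8.3% | 0.255 | 7.6% |
| 30% | 0.210 | 15.1% | 0.231 | 12.4% |

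**If the limit is 4 of 27.** In case A, the single-stage chance of at most 4 events goes from 5.9% with no loss to 10.9%, 18.8% and 30.2%. Under the reconstructed two-stage rule, false success goes from 4.9% to 9.2%, 16.0% and 25.9%.

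**The case against.** A reader might infer that the patients most likely to perforate do leave before the endpoint can be counted, and that the rate is therefore biased. The documents do not support that.

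- Section 2.5 never says that observation for perforation ends at withdrawal, or that withdrawn patients are excluded or counted as event-free. Its opening sentence also speaks of interrupted or shortened treatment, so the wording is ambiguous rather than a clear rule that ends follow-up.
- Section 2.8 sets the perforation window without an exception for withdrawn patients. It also plans quality-of-life, pain and progression assessments at 2 years, and section 2.3 asks for willingness to complete follow-up.
- A perforation that is itself the safety event has already happened and can be counted. Criterion 1 matters only for safety events that precede a perforation.
- The article does not state that progression leads to perforation; that link is inferred. Only criterion 2 plainly selects on toxicity risk.
- At a 10% loss, the exact test still has a type I error of about 4.2%, below the nominal 5%. Part of this room exists because the limit of 3 of 27 is conservative.
- Analysis sets and the handling of missing outcomes may be in the full protocol or the SAP, neither of which is shown.

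All of this stands, and it limits how strongly the point can be put. It does not remove it. The text that is shown names drop-out from the study as the consequence of these criteria, and a site following it could stop looking for perforation.

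**Conclusion.** The point holds in conditional form and is of moderate weight. Section 2.5 merges the end of treatment with departure from the study, and some of its criteria, criterion 2 above all, are related to the primary endpoint and applied by unblinded investigators. If patients withdrawn in this way are not followed to the end of the window, the perforation rate can be biased downward.

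The harm depends on how many are lost. On the exact 5% test, a 10% loss among perforators stays within nominal, while 20% gives about 8% false success and 30% gives 12% to 15%. These figures rest on a true rate of 30%, on assumed losses confined to patients who would perforate, and on a cut-off that the article does not state. No document shows how many patients would be withdrawn, or that any perforation would be missed.

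**What to change.** Amend section 2.5 and add a sentence to sections 2.8 and 2.9:

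1. Meeting a section 2.5 criterion ends protocol treatment only. Follow-up ends early only if the patient withdraws consent to follow-up.
2. Every patient who starts re-irradiation stays in the primary denominator and is followed for perforation through the full section 2.8 window.
3. One sensitivity analysis counts patients lost before the window closes as perforations.

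This leaves untouched when treatment stops and concerns only observation and counting. The cost is protocol wording, follow-up visits for a few withdrawn patients, and possibly a less favourable observed rate.

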### Radiotherapy

2.6

Radiotherapy will be performed using IMRT in 50 Gy /25 fractions. The implementation strategy of PLDR include dividing 2 Gy into 10 fractions, and administering each irradiating dose of 20 cGy at an interval of 3 minutes before the next low-dose irradiation. The actual dose rate of administration each time will be 16.67 cGy/minutes (Fig. 3).

**Figure 3 F3:**
[figure not shown]
Schematic diagram of PLDR segmentation method.

Target contour principle: GTV is defined as all by imaging examinations (esophageal barium meal, CT, esophageal lumen B to exceed, esophageal endoscopy, PET/CT, etc.) found in known generally tumor. GTV includes primary tumor (GTV-t) and enlarged metastatic lymph nodes (GTV-n). The definition of GTV-n is any of the following: the measured value of short diameter >1 cm during the diagnosis of CT scan or less than 1 cm, but met one of the following criteria: PET scan showed high metabolic absorption; lymph nodes fused or clustered; short diameter of tracheoesophageal groove lymph nodes >0.5 cm. In this study, all the enrolled patients were not exposed to preventive irradiation, and there was no need to delineate the clinical tumor volume (CTV). The planned tumor volume (PTV) includes the positioning error due to tissue and organ movement, and PTV= GTV + 0.5 cm. Actual output data can be determined from the quality control data of each center.

### Data collection and management

2.7

A case report by researchers will accompany each case. Mianyang Central Hospital will be responsible for establishing the database and data entry, and will use a data acquisition system and an electronic data management system to manage data. Main researchers will audit the data and will lock it. The final version of the statistical plan will be completed and will be used to analyze the locked data. When the month and the year of treatment are clearly available, but the day is unknown, the date will be recorded as the fifteenth day of the month. When the year is clear, but the day and the month are unknown, the date will be recorded as the intermediate point between the end of the year and the last known date.

### Assessment of the primary and secondary endpoints

2.8

Rate of esophageal perforation is the primary endpoint in this study, which will be observed from the initiation of re-irradiation to 60 days after the end of the study. Esophageal perforation should be diagnosed by esophageoscope. ORR is one of the secondary endpoints in our study. Ninety days after the end of treatment, we will evaluate the efficacy by using the RESICT 1.1 criterion through CT scan and esophageoscope. Quality of life scale QLQ-C30 (V3.0) according to the European Organization for Cancer Research and Treatment (EORTC) and digital pain scale will be assessed to determine the palliative effect on quality of life and pain in 2 years after the end of the study. Kaplan Meier curves will be performed to evaluate TTP, 2 years after the end of the study.

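### The primary event rests on esophagoscopic diagnosis alone, with no provision for perforations shown by other means or fatal before endoscopy, so such events may go uncounted

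*Protocol article*

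**What the plan says.** Section 2.8 of the protocol article names perforation as the primary endpoint, "which will be observed from the initiation of re-irradiation to 60 days after the end of the study". The case definition is one sentence: "Esophageal perforation should be diagnosed by esophageoscope". No other method of confirmation is given, and nothing is said about a perforation seen without endoscopy or a patient who dies before one can be done.

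Three other places bear on this:

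- The Abstract (Introduction) describes the fatal route: "The most serious adverse reactions of re-irradiation include esophageal perforation and hemorrhage caused by esophageal perforation".
- Other examinations that could show a perforation are already in use. Section 2.6 lists "esophageal barium meal, CT" and further imaging for target delineation, and 2.8 assesses response by the RECIST "criterion through CT scan and esophageoscope".
- Section 2.9 sets the comparison. It states that "the incidence of esophageal cancer perforation after re-irradiation is 30"% according to the literature, and expects that with PLDR "the rate of esophageal perforation will decrease to 10"%. The Discussion confirms that results will be set against historical data. How perforation was diagnosed in those sources is not given.

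**The concern.** A case definition tied to one examination counts only the patients who undergo it. Two groups may not. The first is patients whose perforation is already evident on CT or a contrast study. The second is patients who bleed to death or are too ill for endoscopy. On the document's own description, the second group holds the worst events, so the most serious perforations are among the least likely to meet the definition as written.

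The direction of the error matters. This is a single-arm safety comparison in which fewer events means success. No concurrent control arm shares the undercount, so every missed event pushes the result towards the hoped-for 10%. At a true 30%, 27 patients give an expected 27 × 0.30 = 8.1 events, so one or two unclassified cases can decide the outcome. In a multi-center trial without a counting rule, sites may also classify the same case differently.

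**Working it through.** **Inputs from the article (2.9):** historical rate 30%, expected rate 10%, α = 0.05, power 80%, n = 27 read from a table.

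**Inputs assumed, not in the documents:** a share m of true perforations is never endoscoped and so not counted (m = 10%, 20%, one third), and the historical 30% was fully counted.

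**Step 1: reproduce the planned size.** The article states no cut-off. A search over two-stage designs for perforation-free rates of 70% against 90% (α = 0.05, power 0.80) finds the Simon optimal design at exactly n = 27. It treats 6 patients first and continues if more than 4 are perforation-free (at most 1 perforation). It declares success if more than 22 of 27 are perforation-free (at most 4 perforations). Its type I error is 0.0492 and its power 0.804. The planned 27 therefore reproduces and is not in question here. As a second rule, the exact single-stage test at n = 27 with error below 0.05 succeeds at no more than 3 events (error 0.020, power 0.718).

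**Step 2: apparent rate with no treatment effect.** p = 0.30 × (1 − m):

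- m = 10%: 0.30 × 0.90 = 0.27
- m = 20%: 0.30 × 0.80 = 0.24
- m = 1/3: 0.30 × 2/3 = 0.20

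**Step 3: chance of declaring success.**

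Two-stage: P = P(X1 = 0)·P(X2 ≤ 4) + P(X1 = 1)·P(X2 ≤ 3), with X1 ~ Bin(6, p) and X2 ~ Bin(21, p).

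- p = 0.30: 0.1176 × 0.1984 + 0.3025 × 0.0856 = 0.049
- p = 0.27: 0.1513 × 0.2923 + 0.3358 × 0.1413 = 0.092
- p = 0.24: 0.1927 × 0.4083 + 0.3651 × 0.2213 = 0.159
- p = 0.20: 0.2621 × 0.5860 + 0.3932 × 0.3704 = 0.299

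Single-stage: P(X ≤ 3), with X ~ Bin(27, p).

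| Share missed | Apparent rate | False success, two-stage (6 then 27, ≤4/27) | False success, single stage (≤3/27) |
|---|---|---|---|
| 0 | 30% | 4.9% | 2.0% |
| 10% | 27% | 9.2% | 4.2% |
| 20% | 24% | 15.9% | 8.3% |
| one third | 20% | 29.9% | 18.2% |

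A single-stage cut-off of at most 4 in 27 is not used for the headline because its error is already 5.9% with complete counting, above the stated α.

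**The case against.** Endoscopic confirmation is a defensible choice for specificity, and several stronger readings go beyond the text.

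- A reader might infer that a perforation counts only if endoscoped and that all others are scored as no event. The article says only how perforation should be diagnosed. How other cases are classified is left open.
- A reader might infer that day 90 is the only chance to find a perforation, because 2.8 names no other post-treatment endoscopy: "Ninety days after the end of treatment, we will evaluate the efficacy by using the RESICT 1.1 criterion through CT scan and esophageoscope". That sentence concerns response. Perforation is observed from the start of re-irradiation, endoscopy prompted by symptoms is not excluded, and a visit schedule may sit in the full protocol, which is not shown.
- A reader might infer that the day-90 examination falls after the perforation window closes. That requires the 60 days to run from the end of treatment. The text says the end of the study, and on that literal reading the argument fails.
- The 30% comparator may have been ascertained just as narrowly. If so, the bias shrinks or disappears. The documents cannot settle this.
- No passage supports a particular missed share, and no success cut-off is stated, so the magnitudes are hypothetical.

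All five limits stand. They do not remove the core. The article does state a case definition for its primary endpoint, it names one method, and followed as written it leaves imaging-proven perforations and deaths before endoscopy outside the count.

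**Conclusion.** The concern holds in this limited form: the primary event rests on esophagoscopic diagnosis alone, with no rule for perforations shown by other means or fatal before endoscopy. Such events may go uncounted, and in this design the error favours the treatment.

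If one perforation in five were missed, the false-success probability would roughly triple under the two-stage rule, from 4.9% to 16%, and reach 8% under the stricter single-stage rule. At one in ten the single-stage figure (4%) stays below 0.05 while the two-stage figure (9%) does not. These sizes rest on an assumed missed share, on a fully counted 30% comparator and on cut-offs that the article does not state. The direction of the bias is firmer than its size. The planned sample size is unaffected.

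**What to change.** Amend the case definition in 2.8:

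1. For the primary count, include any perforation documented by esophagoscopy or by other objective evidence obtained in the trial or in care (CT, contrast study, surgery, autopsy).
2. Report endoscopy-confirmed perforations as a separate count.
3. Add a sensitivity analysis that counts as events fatal hemorrhage or death with suspected but unconfirmed perforation. These cases should stay out of the primary count, because nothing shows that the historical 30% included them.
4. State what is known of how the 30% was ascertained, so that readers can judge comparability.

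This is a rule for counting outcomes. It needs no added examination and leaves n at 27. The price is that a few less certain events enter the count, and that comparability with the historical rate still depends on how that figure was ascertained.
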